### Statistical analysis

#### Quantitative analysis

All collected individual variables will be described by frequency (%) for categorical variables, and mean (SD) and median (Q1 -Q3) for quantitative variables. The data will be summarized separately in two tables: one for the period before intervention, and another for the period after intervention. The effectiveness of the intervention will be measured comparing the delta of before-after participation rate in intervention area and control areas. Completion time of the exams (screening test and colonoscopy) between intervention areas and control areas before and after the intervention will also be compared. The difference in participation will be analyzed by logistic regression analysis methods taking into account the interactions between the period and area. The influence of other collected variables will be tested using univariate tests (Chi2 or Fisher test for categorical variables and Student or Wilcoxon test for quantitative variables). A multivariate model will be implemented in order to take possible confounding factors into account. Analysis of participation time will be done in two ways: firstly by taking the censored data with a Cox model into account and secondly with a ANOVA model (on the subgroup of patients who participate). The level of statistical significance will be of 5 %.

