### Sample size

We estimated that the intervention would be relevant if it provided an 8 % absolute increase in the colorectal cancer screening participation rate (22 % in the control group and 30 % in the intervention group). With a two-sided α risk of 0.05 and a β risk of 0.1, and assuming an intraclass correlation coefficient for clusters of 0.004 and a mean of 500 patients per cluster (assuming an average of 2000 people per IRIS zone and percentage of people between 50 and 75 years equal to 25 % of the total population), we needed 4 clusters per group (2000 people per group). Taking into account the three groups (one intervention group and two control groups) and stratified by department gives a total number included about 30 000 individuals.

We establish that the number of IRIS zones needed to meet the objectives of the study is 20 intervention IRIS zones and 40 control IRIS zones [24].

So, for each district, we will randomly select:four contiguous intervention IRIS zoneseight control IRIS zones divided into two groups (one adjacent and one distant from the intervention group)

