### Outcomes assessments

#### Primary outcome

To assess the effectiveness of the intervention, the primary outcome will be measured by the difference between before/after participation rates in the intervention zones and in the control zones. Other criteria will be used according to the recommendations made by the National Patient Navigation Leadership Summit (NPNLS) and published in Cancer in 2011 [29]: time to participate, participation in the whole procedure, time to complete the colonoscopy after a positive FOBT test result.

Eighteen months after the beginning of the intervention, each screening management structure, in charge of sending the invitation to individuals included in the mass screening program, will collect the participation status of the men and women included in the study. Each district structure has a database with the contact details of all individuals, eligible to receive an invitation to the national screening program. After the beginning of the intervention, the 18 month-participation rates will be measured, in selected areas. The following items will be measured: program coverage rate (percentage of people guided by navigators), screening participation rate, percentage of patients who get screened after the navigator intervention, colonoscopy completion rate.

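### Time to colonoscopy is compared between areas among FOBT-positive people, a group that navigation itself changes, so a difference in delay cannot be read as an effect on follow-up

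*Protocol article*

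**What the plan says.** Under Primary outcome, the protocol article adds further criteria to the participation rate for judging effectiveness: "time to participate, participation in the whole procedure, time to complete the colonoscopy after a positive FOBT test result". The colonoscopy delay is thus defined only in people with a positive test. The Background section confirms that, in the programme, colonoscopy follows a positive FOBT.

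The Quantitative analysis section then commits to a between-area comparison: "Completion time of the exams (screening test and colonoscopy) between intervention areas and control areas before and after the intervention will also be compared".

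The Primary outcome section also lists items to be measured, among them "percentage of patients who get screened after the navigator intervention, colonoscopy completion rate". No denominator is given for the colonoscopy completion rate, and the analysis section does not say that it will be compared between areas. The whole-procedure criterion has no stated denominator either.

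The description of the intervention says that navigators are to guide invited people to the screening test, and the sample size assumes that they succeed: "22 % in the control group and 30 % in the intervention group".

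**The concern.** Randomising zones makes the invited populations comparable. It does not make the FOBT-positive people comparable, because a person enters that group only by taking the test after the intervention has started, and raising test-taking is what navigation is for. In intervention zones the positives would include people who, without navigation, would not have been tested. Control zones have no counterpart to them.

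A between-area difference in colonoscopy delay therefore has two possible sources: a different mix of people, or a change in how quickly the same people are followed up. The planned comparison cannot separate them. The before/after contrast does not help, because the mix shifts only in intervention zones and only after the start, which is exactly where the contrast looks for the effect. Covariate adjustment is a weak remedy. The article describes navigators collecting socio-demographic information, and it describes no matching collection in control zones.

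Delay is listed among the effectiveness criteria, and the Abstract names complementary exams as well as the FOBT in the programme's main objective. A shift in mix could thus be reported as navigation slowing follow-up, or speeding it up.

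**Working it through.** **1. The plan's own figures.** The inputs, all from the Sample size section, are 22% v 30%, two-sided α 0.05, power 90%, "intraclass correlation coefficient for clusters of 0.004 and a mean of 500 patients per cluster".
- Individually randomised size: 630 per group.
- Design effect: 1 + (500 − 1) × 0.004 = 2.996.
- 630 × 2.996 = 1887 people; 1887/500 = 3.77, rounded up to 4 clusters, or 2000 people per group.
- 4 × 500 × 3 groups × 5 districts = 30 000.

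The stated sample size reproduces and is not in dispute. Only the 22% and 30% are carried forward.

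**2. Share of added people among positives.** Assume that FOBT positivity is the same in usual and added participants, so that it cancels:

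(30 − 22)/30 = 8/30 = 26.7%.

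**3. Effect on mean delay.** Let d_u be the mean delay in usual participants and d_a that in added ones, and suppose that navigation changes nobody's own delay. In intervention zones after the start:

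mean = (22 × d_u + 8 × d_a)/30, a shift of (8/30) × (d_a − d_u).

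The documents give no delays, so these values are assumptions:

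| d_u | d_a | Intervention mean | Control mean | Apparent effect |
|---|---|---|---|---|
| 60 days | 90 days | (1320 + 720)/30 = 68 | 60 | +8 days |
| 60 days | 120 days | (1320 + 960)/30 = 76 | 60 | +16 days |
| 60 days | 60 days | 60 | 60 | 0 |
| 60 days | 30 days | (1320 + 240)/30 = 52 | 60 | −8 days |

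**4. The before/after contrast.** If both areas start at 22% with the usual mix and control zones stay there, the contrast is (intervention after − intervention before) − (control after − control before) = (8/30) × (d_a − d_u) − 0. The whole shift remains.

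**5. Completion rate, only if it were compared among positives.** The article does not state this comparison. Assume 90% completion in usual participants and q in added ones. Completion among intervention positives is then (22 × 0.90 + 8q)/30, and the ratio of completed colonoscopies per invited person is (22 × 0.90 + 8q)/(22 × 0.90).

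| q | Completion among positives | Change from 90% | Per-invited ratio |
|---|---|---|---|
| 0.80 | 26.2/30 = 87.3% | −2.7 points | 26.2/19.8 = 1.32 |
| 0.70 | 25.4/30 = 84.7% | −5.3 points | 25.4/19.8 = 1.28 |
| 0.60 | 24.6/30 = 82.0% | −8.0 points | 24.6/19.8 = 1.24 |

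**6. What per-invited measures can hide.** With unchanged completion, uptake alone gives a ratio of 30/22 = 1.36. From a 90% baseline, completion among positives could fall to 0.22 × 0.90/0.30 = 66% before colonoscopies per invited person showed any loss. At an assumed 3% positivity, a fall in completion from 90% to 82% moves a whole-procedure proportion over all invited people by only 0.30 × 0.03 × 0.08 = 0.07 percentage points.

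**The case against.** The best case against the point has four parts.

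- **Completion rate.** A reader might infer that completion as well as delay is compared between areas among positives. The text does not support that. The analysis section names completion time; the rate appears only as something to be measured, with no denominator. This part of the objection stands, and the point about completion is conditional.
- **Only among positives.** A reader might also infer that all the colonoscopy evidence is confined to FOBT-positive people. The whole-procedure criterion could be taken over everyone invited, and an article may leave such a denominator to the full protocol. This stands too. The finding rests on the stated delay comparison, not on a missing definition.
- **Direction.** It is tempting to say that an effective programme would appear to worsen follow-up. That requires added participants to follow up less well and navigators' help with later exams not to offset it. The documents give no positivity, completion or delay figures, so no direction can be asserted.
- **The alternative.** Per-invited measures mostly repeat the uptake result and could mask worse follow-up, as step 6 shows. Whether people with a positive test reach colonoscopy promptly is a proper question. This stands, and it is why the figures among positives must be kept.

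None of this makes the FOBT-positive people in the two areas comparable. The difficulty lies in a comparison that the article states.

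**Conclusion.** The point holds for colonoscopy delay. The planned between-area comparison is conditional on a positive FOBT, which occurs after allocation and which navigation is meant to make more frequent. Under the plan's own participation rates and equal positivity, about 27% of intervention-zone positives would have no counterpart in control zones.

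The resulting distortion is 8/30 of the difference in delay between added and usual participants: 8 to 16 days for assumed differences of 30 to 60 days, nil if there is no difference, and of opposite sign if added participants are faster. The completion rate would suffer in the same way if it were compared between areas among positives.

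The participation outcome, its analysis and the sample size are not touched. Priority is low to moderate.

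**What to change.** - Make the between-area evidence on follow-up a comparison over all invited people: the proportion who complete the whole procedure (negative FOBT, or positive FOBT followed by colonoscopy), and colonoscopies completed after a positive FOBT per 1000 invited. Use the same period-by-area model as for participation.
- Keep delay and completion among FOBT-positive people, by area and period. Label them a non-randomised, descriptive comparison that is not evidence of a navigation effect on follow-up.
- Report both sets together, and say that the per-invited figures largely reflect uptake and can mask worse follow-up among positives.

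The cost is mainly analysis wording. The screening structures hold the list of people eligible for invitation. The article already plans to measure colonoscopy completion and time to colonoscopy, so the new measures appear to need no further data. That the structures themselves hold colonoscopy status is an inference and should be confirmed. The price is that the trial gives up a formal between-area test of delay.

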## Methods/Design

### Study design

COLONAV is a population-based cluster randomized control study. It assesses the effectiveness of an intervention previously described and evaluated in another cultural environment and in another health care system, as regards CRC screening attendance.

Three parallel groups will be compared:one experimental group with interventiontwo control groups without intervention

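### No named analysis accounts for the IRIS-zone clusters that the design and sample size rely on, so the 5% level of the primary test is not assured

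*Protocol article*

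**What the plan says.** The Study design section is explicit about the unit of allocation: "COLONAV is a population-based cluster randomized control study". The Sample size section selects IRIS zones at random within each of five districts and arrives at "20 intervention IRIS zones and 40 control IRIS zones". The calculation compares "22 % in the control group and 30 % in the intervention group", sets the errors as "With a two-sided α risk of 0.05 and a β risk of 0.1", and allows for clustering by "assuming an intraclass correlation coefficient for clusters of 0.004 and a mean of 500 patients per cluster". Its result is "we needed 4 clusters per group (2000 people per group".

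The primary outcome is the before/after change in participation, compared between intervention and control zones. For its analysis the Quantitative analysis section states: "The difference in participation will be analyzed by logistic regression analysis methods taking into account the interactions between the period and area". It adds chi-square, Fisher, Student and Wilcoxon tests for the influence of other variables, and a multivariate model for confounding. Time to participation is analysed in two ways: "firstly by taking the censored data with a Cox model into account", and then by ANOVA among those who participate. The significance level is 5%. No random effect, generalised estimating equation (GEE), robust variance, frailty or cluster-level analysis appears in the section.

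**The concern.** The design and the sample size treat residents of a zone as correlated. The analysis section names its models, says what the primary model takes into account and sets the significance level, but leaves the zones out.

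The interaction does not fill the gap. In that section, area distinguishes intervention from control territory, so period by area is the treatment effect itself. Zone effects that stay constant over time cancel in a before/after difference. Zone effects that shift between periods do not cancel: they add to the variance of the tested term, and a model for independent individuals does not see them. At stake are the width of the confidence interval and the false-positive rate of the primary test, and likewise any comparison of completion times between areas.

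**Working it through.** **1. Reproduce the sample size.** Inputs from the Sample size section: 22% versus 30%, two-sided α 0.05, power 0.90, ICC 0.004, m = 500.

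- Individuals per group without clustering: [1.96·√(2·0.26·0.74) + 1.2816·√(0.22·0.78 + 0.30·0.70)]² / 0.08² = 630.
- Design effect: 1 + (500 − 1)·0.004 = 2.996.
- 630 × 2.996 = 1887, and 1887/500 = 3.77, so 4 zones or 2000 people. This matches the article.
- Total: 3 groups × 5 districts × 4 zones × 500 = 30 000. This also matches.
- Without the design effect, 630/500 = 1.26, so 2 zones would have been enough. The stated 4 zones rest on clustering being counted.

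**2. Comparison of areas in one period, zones ignored.** This is the comparison for which the trial was sized.

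- Standard error too small by √2.996 = 1.73.
- True α = 2·[1 − Φ(1.96/1.73)] = 25.7%.

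**3. The before/after interaction, zones ignored.** Two quantities that the article does not give are needed, and both are assumptions here:

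- CAC: the correlation of a zone's effect between the two periods.
- ρ: the correlation between a person's two outcomes, if the same people are observed in both periods (ρ = 0 if they are different people).

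The ratio of true to assumed variance is (1 − ICC)(1 − ρ) + m·ICC·(1 − CAC) = 0.996·(1 − ρ) + 2·(1 − CAC). The true level is 2·[1 − Φ(1.96/√ratio)].

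| CAC | Ratio, different people | True α | Ratio, same people (ρ = 0.4) | True α |
|---|---|---|---|---|
| 1 | 0.996 | 5.0% | 0.598 | 1.1% |
| 0.9 | 1.196 | 7.3% | 0.798 | 2.8% |
| 0.8 | 1.396 | 9.7% | 0.998 | 5.0% |
| 0.5 | 1.996 | 16.5% | 1.598 | 12.1% |
| 0 | 2.996 | 25.7% | 2.598 | 22.4% |

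**4. Check by simulation.** The logistic interaction test was simulated with 20 intervention and 40 control zones of 500, different people in each period, no treatment effect, 22% participation and 20 000 replicates per setting. It rejected in 5.0%, 7.1%, 10.0%, 16.6% and 25.2% of replicates at CAC 1, 0.9, 0.8, 0.5 and 0. The single-period comparison rejected in 26.3%. These agree with the formula.

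**5. Tests of other variables.** For an individual-level covariate the design effect is roughly 1 + (m − 1)·ICC of covariate·ICC of outcome. With an assumed covariate ICC of 0.05 this is 1 + 499·0.05·0.004 = 1.10, which is small.

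**The case against.** The strongest reply is that silence is not a decision. The article refers to logistic regression methods in general terms, which can include mixed or GEE logistic models. Its authors plainly knew of the clustering, and a journal article condenses a fuller plan. This stands in part: a reader might infer that the zones will deliberately be ignored in an ordinary logistic model, and the text does not say so. But the section is not merely brief. It states what the primary model takes into account, names the time-to-event models and fixes the level, all in individual-level form. A reader who follows it would not carry out the analysis that the sample size assumes.

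A second reply is that the 26% figure is not about the primary test. That is correct. It belongs to a single-period comparison, whereas the primary contrast is a difference of changes in which stable zone effects cancel.

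A third is that standard errors need not be too small. That is also correct. The programme re-invites residents every two years, so overlap between the before and after populations is plausible. Ignoring the correlation within people makes the interaction test conservative, and with stable zones the level falls below 5%.

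Two further inferences are not supported. One is that every test in the section is materially invalid: the chi-square and Student-type tests concern other variables, not the comparison of areas, and their inflation is likely to be small. The other is that inflation can be computed for a block of four zones because the intervention zones are contiguous and each district has one navigator. The unit of correlation may indeed be larger than a zone, but the article gives no ICC at that level.

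**Conclusion.** The point holds as a conflict between the analysis section and the design and sample size. Zones are allocated and budgeted for with a design effect of 3.0, yet no named model accounts for them, so the 5% level is not assured. For the primary interaction the true level runs from 5.0% (CAC 1) to 25.7% (CAC 0) with different people in each period, and is about 7% to 17% for CAC 0.9 to 0.5. With the same people observed twice and an assumed ρ of 0.4, it is about 1% to 12% for CAC 1 to 0.5.

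The ICC and zone size are the protocol's own; CAC, ρ and the degree of overlap between the two populations are assumptions. An inflated level is therefore likely but not proven for the primary test. It is clear only for a comparison of areas within one period. Because the validity of the primary test is affected and the remedy is wording, this should be fixed before analysis.

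**What to change.** In the Quantitative analysis section, state that the primary period-by-group interaction is estimated with a method that accounts for zone and zone-by-period variation, with district as a stratum. Suitable options are a mixed-effects logistic model or GEE with a small-sample correction, or a cluster-level analysis of the before/after change in zone participation rates. Apply the same to the multivariate model. State whether the same people can contribute to both periods and, if so, how that dependence is handled. In the Cox model use a shared frailty or a cluster-robust variance, and include a zone effect in the ANOVA.

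The cost is analysis wording and wider confidence intervals where zone-by-period variation exists. No new data are needed. The sample size already allows for clustering: for the single-period comparison it describes, 2000 people per group with a design effect of 2.996 gives about 91.6% power by the normal approximation.

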### Selection of study sites and participants

The study will include men and women aged from 50 to 74 years old, invited to screening and living in underserved areas. The research will be conducted in the following five districts because of their different socioeconomic characteristics:A rural district (L’Ardèche, 313 578 inhabitants)A district with an industrial economy and low development (La Loire, 746 115 inhabitants)A district with a tertiary economy and high development (Le Rhône, 1 708 671 inhabitants)A district where CRC screening has been implemented for a long time (La Côte d’Or, 524 144 inhabitants)One of the suburban districts of the capital (Le Val-de-Marne, 1 318 537 inhabitants)

In each district, the geographical areas to be studied will be determined by matching the criteria in terms of the socioeconomic indicators and the low participation rate for CRC screening. In France, each district is divided into IRIS zones, ie aggregated units for statistical information used as a system for dividing the country into units of equal size (2000 residents per basic unit). We will use the French European Deprivation Index (EDI) [23] to determine the most deprived IRIS zones (quintiles 4 and 5 of the Index corresponding to the most disadvantaged areas) and the participation rates of each zone to select the lowest ones.

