**Fig. 1 Fig1:**
[figure not shown]
Conceptual model of patient navigation (Fiscella 2011)

The main role of the navigators is to promote CRC screening among the target population to increase participation rates in these areas. The missions of the navigators are to contact individuals living in the intervention area and invited by the screening structure and to guide them to the realization of the screening test.

Navigators’ activities will be: 1) to establish partnerships with local associations, religious places, health centers, health fairs, GPs… in order to participate in local events and to meet the target population 2) to find a committee room to meet people who are in need 3) to communicate by phone or face-to-face with the target population 4) to provide personalized assistance to each person in order to help them to overcome obstacles in the realization of the screening test (psychological, financial or logistical barriers) 5) to collect patient socio-demographic information.

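### Zones are chosen within five deliberately different districts, but the stated effectiveness model names only period and area, and adjustment appears to rest on univariate tests of an undefined pool of variables

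*Protocol article*

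**What the plan says.** **Design.** Under Selection of study sites and participants: "The research will be conducted in the following five districts because of their different socioeconomic characteristics". One of the five is singled out because screening has run there for a long time. Under Sample size, the calculation is "stratified by department gives a total number included about" 30 000 people, and the draw is made district by district: "So, for each district, we will randomly select" four contiguous intervention zones and eight control zones, the latter split into an adjacent and a distant group.

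**Model.** Under Quantitative analysis, effectiveness is the before/after change in participation compared between intervention and control areas. It is analysed by logistic regression with a period-by-area interaction. District is not mentioned, nor is the zone as a cluster.

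**Covariates.** The same paragraph continues: "The influence of other collected variables will be tested using univariate tests" (chi-square or Fisher, Student or Wilcoxon). The next sentence reads: "A multivariate model will be implemented in order to take possible confounding factors into account". No covariates are listed.

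**Where individual data come from.** Under Study groups, Patient navigation intervention, one navigator activity is "to collect patient socio-demographic information", and navigators work with residents of the intervention area. Under Secondary outcome, the questionnaires go to people in contact with navigators. For all zones, the Primary outcome section names the screening structures' databases, mentioning contact details and participation status.

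**The concern.** The design uses district as a stratum, and the analysis as written does not. Each district has its own screening structure, and one has a long screening history, so participation could drift differently from district to district between the two periods. If it does and the model ignores it, that drift is counted as unexplained variation between zones, and a zone-level test becomes less sensitive than the design allows.

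The covariate wording raises a separate difficulty. Read in order, the two sentences suggest that variables are tested one at a time and then carried into an adjusted model. If so, the adjusted estimate depends on which variables happen to reach significance. If not, the text gives no basis for choosing confounders.

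The pool is described only as other collected variables. The one socio-demographic collection in the article is done by navigators, in the intervention zones, after the intervention has begun. Such variables would be absent by design in control zones and in the before period. Adjusting for them would either drop the comparison group or condition on having been contacted.

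**Working it through.** **1. The plan's own sample size.** Inputs from Sample size: 22 % "in the control group and 30 % in the intervention group"; "With a two-sided α risk of 0.05 and a β risk of 0.1"; intraclass correlation 0.004; 500 people per zone.

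- Unclustered n per group = [1.96·√(2·0.26·0.74) + 1.2816·√(0.22·0.78 + 0.30·0.70)]² / 0.08² = 629.7, so 630.
- Design effect = 1 + 499·0.004 = 2.996.
- 630 · 2.996 = 1887; 1887 / 500 = 3.77, so 4 zones (2000 people) per group.
- Total = 4 zones · 3 groups · 5 districts · 500 = 30 000, with 20 intervention and 40 control zones.

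Every stated figure reproduces. Nothing below changes them.

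**2. Does omitting district bias the contrast?** The simulation used 5 districts, 4 intervention and 8 control zones in each (the two control groups pooled), 500 people per zone and two periods. The true log odds ratio is log[(0.30/0.70)/(0.22/0.78)] = 0.418. The zone SD on the logit scale is √(0.004/(0.22·0.78)) = 0.153, with half of that variance assumed to be zone-by-period. There were 400 replicates per row.

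| Assumed between-district SD (logit) | Mean estimate, no district terms | Mean estimate, district main effects |
|---|---|---|
| 0 | 0.418 | 0.418 |
| 0.2 | 0.414 | 0.417 |
| 0.4 | 0.405 | 0.415 |

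The equal 4:8 split keeps stable district differences almost wholly out of the before/after contrast.

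**3. Does it cost precision?** This scenario adds district-specific trends with an assumed SD of 0.2 on the logit scale. Zone-level before/after changes were analysed with and without district, 1000 replicates each. A district term in an analysis of changes plays the part of district-by-period in a two-period model.

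| | Without district | With district |
|---|---|---|
| Type I error (nominal 5%) | 2.0% | 5.2% |
| Power at odds ratio 1.2 | 68.5% | 87.3% |

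Monte Carlo standard errors are √(0.685·0.315/1000) = 1.5 points and √(0.873·0.127/1000) = 1.1 points for the two powers.

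Hand check of the two powers:

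- Within-district variance of a zone's change = 2·(0.0233/2) zone-by-period + 2·1/(500·0.1716) sampling = 0.0233 + 0.0233 = 0.0466.
- Standard error = √(0.0466·(1/20 + 1/40)) = 0.0591, and log 1.2 = 0.1823.
- Power with district ≈ Φ(0.1823/0.0591 − 1.96) = Φ(1.12) = 0.87.
- Without district, the test uses variance 0.0466 + 0.04 = 0.0866, so its standard error is 0.0806 and its critical value 1.96·0.0806 = 0.158. The true spread of the estimate is still 0.0591, so power ≈ Φ((0.1823 − 0.158)/0.0591) = Φ(0.41) = 0.66.

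The hand figures are close to the simulated ones. They hold the district variance at its assumed value, although with five districts it varies from sample to sample.

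With no district-specific trends, the zone-level powers with and without district were within half a point of each other (for example 87.0% and 86.8% at a district SD of 0.2).

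**4. Zone clustering.** A logistic model that treats individuals as independent had a type I error of about 15 to 17%, with or without district main effects, when half the zone variance was zone-by-period. It was 4.7% when none was. District terms therefore do not replace an allowance for zone-level variation.

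**The case against.** The strongest reply is that silence is not exclusion. A journal article condenses the plan; the regression sentence does not say that period and area are the only terms, and the multivariate model could contain district. That stands, and it is why the request is to write the terms in. Still, the article does state a model and a covariate procedure, and neither follows the design it describes.

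Three stronger readings are tempting, and the documents do not support them.

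- *Large loss of precision.* A reader might compare zone rates in the after period alone. Zone variance is then 0.004·0.22·0.78 plus 0.1716/500, or 10.3 squared percentage points. Assumed district SDs of 3 or 5 points would inflate the standard error by √(19.3/10.3) = 1.37 or √(35.3/10.3) = 1.85. The arithmetic is right, but the primary outcome is a before/after difference, from which stable district differences largely cancel. Those factors do not apply here.
- *Univariate tests decide which covariates enter.* The order of the sentences suggests it, but no entry rule or threshold is stated.
- *Navigator-collected data will be used for adjustment.* The article does not say so. It plans separate before and after tables of the collected individual variables, which fits data held in both periods. Nor does it say that the screening databases lack fields such as age and sex. What remains is that the pool is not limited to data held for all zones.

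**Conclusion.** The concern holds in a limited form. The stated model does not name the stratum within which zones are selected, and the basis for covariate adjustment is poorly fixed. Omitting district causes little bias in the before/after contrast. The effect of the omission is a conservative and less powerful zone-level test if trends differ by district: about 69% power against 87% at an odds ratio of 1.2, with type I error of 2.0% against 5.2%. Those figures rest on an assumed district-trend SD of 0.2 (logit), an assumed even split of the zone variance and pooled control groups; the documents give none of these. With no difference in trends, the loss is negligible. At the planned effect of 22% against 30%, simulated power was 100% with and without district in the scenarios run (which had no district-specific trends), so the issue bears on smaller effects. That covariates are selected by significance, or that one-arm data enter the model, is an inference from the wording and not a stated plan.

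**What to change.** In the Quantitative analysis section:

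1. Add district and district-by-period terms to the primary period-by-area model, with an allowance for clustering by zone consistent with the intraclass correlation in the sample size.
2. Drop univariate testing as a basis for adjustment. Name a short covariate list in advance, restricted to variables held for all zones in both periods: for example age, sex and the zone deprivation index, if the screening databases hold the individual items. Use prior participation only if it refers to a round before the before period; otherwise it overlaps with the outcome being contrasted.
3. State that navigator-collected variables serve only to describe the people contacted.

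This is a change of wording. In a zone-level analysis of changes, the residual degrees of freedom fall from 60 − 2 = 58 to 58 − 4 = 54. Sample size and number of zones are unaffected.
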